### Sequence generation

As described in the Section of study population all the households in the district are eligible to the treatment. The unit of randomization is the sub-village (*sub-kebele*) level. For this study, we divided the 30 villages *(Kebeles)* into 66 sub-villages/sub-kebeles. In each sub-kebele, we will obtain a fresh list of farmers, which are organized into one-to-five groups.^1^ Each *sub-kebele* will be randomly assigned into the four treatment arms.

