### Randomization

As the study area is composed of different localities (and elevations) of the district, the risk of malaria infection also varies among *kebeles* (document review from district malaria information). Therefore, the study area will be first clustered into *kebeles* and then each kebele will be clustered in to *sub-kebeles*. The randomization process will be conducted using the STATA’s *sampsi* package and using *sub-kebele* as a unit of randomization. Efforts will be made to ensure that each *kebele* receives balanced number of treatments following the standard protocol developed by Pinder et al. (2016) [14]. Stratified randomization by *sub-kebeles* will take out the kebele effect and the likelihood of chance imbalances between study arms. All entomological, epidemiological, and social studies will be conducted following the same rule described above i.e., stratified randomization. The randomization will be done by ZA to prevent selection bias by concealing the allocation sequence from the field researchers assigning sub-kebeles into the four treatment arms until the moment of assignment. Thus, both the chief investigator and the principal investigator will not be involved in the randomization process.

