### Statistical methods

#### Malaria incidence data analysis

Change in clinical malaria incidence over 2 years period among the treatment and control arms will be determined using Poisson distribution. In this trial we will follow modified ITT protocol and if a child is lost from follow up, or withdraw from the study, or refuse to be included in the treatment, it will be immediately replaced by a child from the reserve list. The Relative Risk (RR) and RR Reductions (RRR) will be calculated with corresponding 95% confidence intervals to compare dichotomous variables, and difference in means will be used for additional analysis of continuous variables. Mixed effects Poisson model will be used to test the difference in incidence rates among the study arms, to determine effects of the repeated measurements within house, village, the effect of year and village-intervention interaction effects. To control the effect of clustering or village and individual level confounding factors such as gender and age, these covariates will be fitted in to random effects during analysis. If a child is diagnosed with malaria case within 28 days of the first episode with the same plasmodium species, then it will be put on treatment as part of the safety protocol, however, the case will not be included in the analysis. The prevalence of anaemia among the study participants (children) will be analysed using the guideline developed by world health organization [47]. Accordingly, all children between 6 and 59 months of age, whose Hb level is recorded between 10.0–10.9 g/dl, 8.0–9.9 g/dl and less than 8.0 g/dl will be graded as mild, moderate, and severe, respectively. In line with this we will also report community level anaemia prevalence. Thus, a prevalence of anaemia will be stated as severe if it is documented over 40% (combining mild, moderate, and severe) and moderate if the prevalence is 20–39.9%. Both malaria and anaemia prevalence data will be compared in the intervention and control houses using multilevel mixed-effects logistic regression models, taking village effects into account.

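### The incidence model sets out to determine village-by-intervention interaction, which under sub-kebele randomisation cannot be separated from ordinary variation between sub-kebeles

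*Protocol article*

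**What the plan says.** Under Statistical methods (Malaria incidence data analysis), a mixed effects Poisson model is to test the difference in incidence between arms and to determine the effects of repeated measurements within house and village, together with "the effect of year and village-intervention interaction effects". House and village are the levels named. No sub-kebele term appears. The next sentence says that clustering or village factors, together with gender and age, will go into random effects. The article does not say whether the interaction is a fixed or a random term.

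On the design, Sequence generation states that "The unit of randomization is the sub-village" (sub-kebele), that "we divided the 30 villages *(Kebeles)* into 66 sub-villages/sub-kebeles", and that "Each *sub-kebele* will be randomly assigned into the four treatment arms". The Randomization section repeats the sub-kebele as the unit and aims to balance treatments within each kebele. The flow-chart section explains the unequal arm sizes by the differing numbers of households per sub-village, which fits allocation of whole sub-villages.

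Two places say otherwise. The Abstract (Methods) names the household as the unit, and the opening of the Study flow chart section has treatments assigned to households with village as the blocking factor.

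**The concern.** A village-by-intervention interaction asks whether the effect of an arm differs between villages. To answer that, a village needs replication within arm at the level that was randomised. If a whole sub-kebele receives one arm and a village has only two or three sub-kebeles, there is no such replication. A sub-kebele with unusually high or low malaria risk then looks like a village in which the intervention failed or succeeded.

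The Background argues that efficacy may depend on epidemiology and agro-ecology, and the Conclusion directs the findings to national malaria control programmes. An apparent finding that screening or push-pull works in some villages and not in others could therefore carry weight.

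**Working it through.** **Inputs from the protocol.** 30 kebeles, 66 sub-kebeles, four arms; 167 + 246 + 250 + 175 = 838 households, one child each, followed for two years. The arm sizes reproduce the stated total. The point does not depend on how 838 was derived.

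**Cell counts under sub-kebele randomisation.**
- Sub-kebeles per kebele: 66 / 30 = 2.2, against four arms.
- Village-by-arm cells: 30 × 4 = 120.
- If the sub-kebeles of a kebele receive different arms, 66 cells are filled, each by exactly one sub-kebele, and 120 − 66 = 54 are empty.
- With unrestricted allocation instead, about 56 cells are filled and 82% of those hold a single sub-kebele (simulated, assuming 24 kebeles with two sub-kebeles and 6 with three; 24 × 2 + 6 × 3 = 66).

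**Degrees of freedom.** Between-sub-kebele contrasts within kebeles: 66 − 30 = 36. The arm main effect uses 3, which leaves 33. With different arms within each kebele, these 33 are the whole interaction and also the whole between-sub-kebele residual. The two are aliased whatever the incidence or the amount of cluster variation.

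**Under the household reading.** 838 / 120 = about 7 households per village-by-arm cell. The interaction is then separable in principle.

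**Size, if the term is fitted as a fixed effect and tested.** The protocol gives no between-sub-kebele variation and no incidence rate for the cohort, so both are assumed:
- Layout: 24 kebeles with two sub-kebeles and 6 with three, different arms within a kebele, no arm effect and no true interaction.
- Children per sub-kebele: 838 / 66 = 12.7, giving 12.7 × 2 = 25.4 child-years.
- Rates per child-year: 0.11 (borrowed from the 11% annual parasite figure in Study setting), 0.22 (sensitivity), and 0.028 (borrowed from the 2.8% prevalence used as the sample-size benchmark; prevalence is not incidence, so this only extends the range). Expected episodes per sub-kebele: 25.4 × 0.11 = 2.8; 25.4 × 0.22 = 5.6; 25.4 × 0.028 = 0.7.
- Test: Pearson goodness of fit of the Poisson model with kebele and arm, which is equivalent to testing the saturated interaction, at nominal 5%.

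| Rate per child-year | CV 0 | CV 0.25 | CV 0.5 |
|---|---|---|---|
| 0.11 | 3–5% | 10–16% | 60–66% |
| 0.22 | 3–5% | 27–34% | 93–95% |
| 0.028 | – | 2–8% across both CVs | 2–8% across both CVs |

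The ranges span repeated runs with a few hundred replicates per setting. A likelihood-ratio version at 0.2 per child-year shows the same rise (10%, 48% and 95% at CV 0, 0.25 and 0.5). At lower rates it already exceeds nominal at CV 0 because counts are sparse, so the Pearson figures are the better guide.

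**What deleting the term would do.** In the same layout, the arm comparison from a Poisson model with kebele and arm only, and so with no term for the randomised unit, has a false-positive rate of about 8–17% at CV 0.25 and 20–42% at CV 0.5, for rates of 0.11–0.22.

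**The case against.** The best defence is that the model is a mixed model and the sentence that follows places clustering factors in random effects. Read that way, village-by-intervention is the variance component for the randomised sub-kebele, and so the right error term for the arm comparison. The word for testing attaches to the difference between arms; no test of the interaction is announced. This largely stands. Having the term in the model is not the fault. What remains is that the sentence lists it beside the year effect as something to determine, and the stated design cannot do that.

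A reader might infer that the test would usually come out significant. The figures do not support this: at CV 0.25 it rejects in about a third of trials or fewer, and at 0.028 per child-year it is near nominal. Nor does the protocol say that risk varies between sub-kebeles within a kebele. The Randomization section speaks of risk varying among kebeles, which stratification addresses, so the CVs are purely assumptions.

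A reader might also infer that village-specific effects will be published. No objective, clinical endpoint or planned paper says so. The reporting risk is a reading of the word determine, not a stated intention.

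Finally, the design is contested within the article. If the household is the unit, the aliasing does not arise. That stands as a condition on the point. The sections that describe the allocation procedure, and the explanation of the arm sizes, nevertheless favour the sub-kebele.

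**Conclusion.** The point holds, conditional on the sub-kebele being the unit of randomisation. The stated interaction then cannot be estimated as effect modification, because its 33 degrees of freedom are the between-sub-kebele residual. That conclusion needs only the counts of kebeles, sub-kebeles and arms, and arms that differ within a kebele; under unrestricted allocation it is nearly as strong.

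The inflated error rate is a further and weaker conclusion. It applies only if the term is fixed and tested, and it depends on assumed incidence and cluster variation: from near nominal in the low-incidence case to above 90% at CV 0.5 with 0.22 episodes per child-year. The documents do not establish that such a test is planned. This is a correction to one phrase of the analysis section that is worth making, not a failure of the primary arm comparison.

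**What to change.** 1. Reconcile the unit of randomisation across the Abstract, Study flow chart, Sequence generation and Randomization sections.
2. If it is the sub-kebele, replace the interaction phrase in Malaria incidence data analysis with a sub-kebele random effect, named as the error term for the arm comparison. State that it is not interpreted or reported as a village-specific intervention effect.
3. Do not simply strike the phrase. The section names no other term for the randomised unit, and the arm comparison would become anti-conservative.

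The cost is one or two sentences and no new data. What is given up is any claim about effects in individual villages, which this design could not support.

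If the household proves to be the unit, step 2 does not apply and the aliasing argument falls away.

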## Methods

### Study setting and period

This study will take place between September 2020 and December 2022 in the Jabi-Tehnan district of Amhara regional state, Northwest Ethiopia. The capital town is Finote-Selam, which is about 387 km from the National capital, Addis Ababa, and 176 km Southwest of the regional capital, Bahir Dar. The population of the district was 211,516 in 2017 with an average annual growth rate of 2.8% [32]. The district is divided into 38 villages *(Kebeles),* which is the lowest administrative unit of the country, and three town administrations. More than 90% of the people in the district live in rural areas practicing mixed farming.

The altitude of the district ranges from 900 to 2300 m above sea level. Much of the area lies in the higher altitude range, closer to 2300 m. Agro-ecologically, 88% of the district is classified as mid land and the remaining 12% as low land. The topography of the district is dominated by areas of flat plain. According to Asmare & Gure, 2019 [33], the topography is classified as 65% flat plain, 15% mountainous, 15% undulating and 5% valley. The rainfall distribution is uni-modal, and the rainy season normally lasts for 4 months from mid-May to mid-September. The annual rainfall ranges 1250 mm per annum. The mean minimum and maximum temperatures are 14 °C and 32 °C, respectively [33]. According to the report compiled from 17 villages *(Kebeles)* of the district, malaria is a major health problem threat resulting in total mortality of 4345, and average Plasmodium annual parasite rate (API) of 11% ([name] 2018, personal communication). A cross sectional active malaria prevalence survey from randomly selected kebeles of the district in 2013 showed the disease prevalence of 2.8% [34]. According to the preliminary information collected from the district, houses are made of walls plastered with mud and roofs covered with corrugated iron sheet. According to the baseline survey conducted in the area 59% of the respondents reported that they keep the livestock in the same house but in separate rooms [35].

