### Data collection and management

#### Data collection methods

For this study, each household will be provided with a specific identification (ID) number. The child included in the study from each household will receive a unique personal, three-digit ID number (village number/household number/person number). All forms and datasets will identify participants by their unique identifier numbers, and names will not be used. The geographic coordinates of all study households will be documented at the beginning of the study and used in mapping the study points. Questionnaires and forms used will be initially prepared in English and translated into Amharic for data collection and then it will be translated back to English later. The questionnaire has already been validated. We will use the questionnaire for collection of the malaria KAP, socio-economic, socio-demographic, the acceptance of HS, challenges related to HS utilization, LLINs ownership and utilization. There are questions pertaining to PPT acceptance, utilization, and other opinion. Databases will be password protected and accessible only to authorized personnel. All documents will be securely stored in locked filing cabinets and accessible only to authorized personnel.

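### The malaria models leave out elevation, which the plan names as a driver of risk and which kebele blocking cannot fully remove with 66 sub-kebeles, 30 kebeles and four arms; the loss is a modest amount of precision

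*Protocol article*

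**What the plan says.** On the source of risk, the Randomization section states: "As the study area is composed of different localities (and elevations) of the district, the risk of malaria infection also varies among" kebeles, and gives as its basis a "document review from district malaria information". It then says that stratification will deal with the kebele effect and with chance imbalance between arms. Under Study setting and period: "The altitude of the district ranges from 900 to 2300 m above sea level". The section on the entomological sample places the treatment households in three zones: low, mid and high land.

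On the data, Data collection methods says: "The geographic coordinates of all study households will be documented at the beginning of the study and used in mapping the study points". No other use of the coordinates is given.

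On the analysis, Malaria incidence data analysis fits a mixed-effects Poisson model "to determine effects of the repeated measurements within house, village, the effect of year and village-intervention interaction effects". The next sentence begins "To control the effect of clustering or village and individual level confounding factors such as gender and age" and places these covariates in the random part of the model: "individual level confounding factors such as gender and age, these covariates will be fitted in to random effects during analysis". The malaria and anaemia prevalence comparisons are made "using multilevel mixed-effects logistic regression models, taking village effects into account". Elevation, zone and pre-trial malaria risk appear in none of these models.

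**The concern.** The plan identifies one strong predictor of malaria risk that is fixed before any intervention, and leaves its control to the design. Sequence generation gives about 16 or 17 sub-kebeles per arm (66/4 = 16.5), so mean elevation will differ somewhat between arms by chance. If blocking is incomplete and elevation is not in the model, two things follow. Part of the between-kebele variation stays in the standard error of the arm effect. The particular imbalance that the allocation produces also stays in the estimate.

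The village term does not settle this. As a random intercept it only partly removes kebele differences from the between-kebele part of the comparison. It cannot see elevation differences between sub-kebeles of one kebele, and the sub-kebele is what the plan calls the unit of randomization.

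The same sentence has a second fault. Gender and age are to enter as random effects. They are ordinary covariates whose coefficients should be estimated as fixed effects; a variance component for a factor with two levels is hardly estimable.

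**Working it through.** **1. Can the blocking be complete?** Inputs from Sequence generation: 66 sub-kebeles, 30 kebeles, four arms.

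- Average per kebele: 66/30 = 2.2.
- Give each kebele one sub-kebele; 66 - 30 = 36 remain. A kebele needs three more to hold all four arms, so at most 36/3 = 12 kebeles can be complete.
- At least 30 - 12 = 18 kebeles lack one or more arms. With an even split (24 kebeles with two and 6 with three: 48 + 18 = 66), no kebele holds all four.

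Stratification therefore cannot remove the whole kebele effect, and part of each arm comparison is between kebeles.

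**2. What does elevation add to the planned model?** The plan gives no figure to reproduce here, so the size comes from simulation of cluster-level log-rates: 66 sub-kebeles, 30 kebeles, four arms, 2000 runs per scenario. Assumptions from outside the documents: kebele SD of the log-rate 0.3 to 1.0; elevation explaining 25%, 50% or 80% of kebele variance; sub-kebele SD 0.3. The rate was set at about 0.22 episodes per child over two years (the 11% annual figure under Study setting and period, doubled).

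Variance reduction = 1 - (SE with elevation / SE without)², with the village random intercept in both models.

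| Allocation | Kebele SD | 25% explained | 50% | 80% |
|---|---|---|---|---|
| Arms differ within kebele | 0.3 | 0.243 to 0.243 (0%) | 0.244 to 0.241 (3%) | 0.247 to 0.239 (7%) |
| | 0.6 | 0.254 to 0.251 (2%) | 0.267 to 0.261 (4%) | 0.263 to 0.248 (11%) |
| | 1.0 | 0.271 to 0.268 (2%) | 0.275 to 0.270 (4%) | 0.265 to 0.248 (12%) |
| Unblocked | 0.3 | 0.255 to 0.251 (3%) | 0.253 to 0.246 (6%) | 0.256 to 0.243 (10%) |
| | 0.6 | 0.278 to 0.274 (2%) | 0.280 to 0.268 (9%) | 0.283 to 0.254 (20%) |
| | 1.0 | 0.295 to 0.289 (4%) | 0.288 to 0.277 (7%) | 0.295 to 0.267 (18%) |

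Entries are the SE of the arm effect without, then with, elevation. A 12% lower variance narrows the interval by 1 - √0.88 = 6%; 20% narrows it by 1 - √0.80 = 11%. The mean estimated arm effect under no true effect stayed between -0.011 and 0.011 in every scenario, with or without elevation.

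**3. How large is the chance imbalance?** The difference in mean elevation between two arms had an SD of about 0.27 elevation-SDs (blocked) or 0.34 (unblocked). If elevations were uniform over 900-2300 m, one SD would be 1400/√12 = 404 m, giving about 109 m and 137 m. Study setting and period says that much of the district lies towards the upper end, so these values are probably high.

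**4. Is there another clean baseline adjuster?** The timeline puts house screening in May to July 2020 and the net section puts distribution in July 2020. The baseline clinical survey is in September to October 2020, after both. Elevation is unaffected by the interventions; that survey's results may not be.

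**The case against.** The strongest reply is that the plan already deals with elevation at the level where it names it. Risk is said to vary among kebeles, and kebele is the block, the stratum and a model effect. This largely stands: the village term recovers most of the between-kebele precision, and what elevation adds is small. It does not stand in full, because the blocking cannot be complete.

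A second reply is that a covariate list belongs in the analysis plan and that the wording is open. That would be fair if the article were silent. It states an adjustment set, however, and its open phrase qualifies individual-level factors, which does not naturally reach elevation or zone.

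Several stronger readings are tempting and are not supported:

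- That the models adjust for gender and age alone. Village, house, year and a village-by-intervention term are named for incidence, and village effects for prevalence. Against a model with no village term the gain from elevation would be 2-57%, but that is not the planned model.
- That the omission biases the arm effects. Chance imbalance under randomization is not bias, and the simulated mean effects are about zero.
- That the needed data are already on file. Coordinates are still to be recorded, elevation is not mentioned among the items collected, and the district report described covers 17 villages against 30 in the trial.
- That the gain is reliably 14-28%. That range comes from a generalized least squares calculation that assumes incidence halves per 300 m. The same calculation gives 8-13% per 500 m and 4-6% per 800 m. With most kebeles placed at 1500-2300 m and an incidence of 0.03 per child-year, a comparable calculation gives about 1-18%.
- That imbalance shifts the rate ratio to roughly 0.75-0.91 (a one-SD imbalance: 2^(-125/300) = 0.75; 2^(-105/800) = 0.91). This is the effect before the village term has acted.
- That effect modification by setting is ignored. The Background describes settings for evaluation and plans no subgroup test, and the model does carry a village-by-intervention term.

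**Conclusion.** The point holds as a modest, inexpensive improvement. The plan names elevation as a driver of risk, relies on a stratification that must be incomplete in at least 18 of 30 kebeles, and then leaves elevation and zone out of both malaria models. With the village effect kept, the expected gain from adding elevation is about 0-12% lower arm-effect variance if arms differ within kebeles, and up to about 20% if allocation is unblocked. The gain is in precision and in protection against chance imbalance.

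The count of incomplete kebeles follows from the protocol's own figures. The percentages rest on assumed kebele variation and an assumed elevation gradient, neither of which the documents give. The point also takes the sub-kebele as the unit of randomization, as Sequence generation and Randomization state. The Abstract and the Study flow chart section speak of households, and if households were truly randomized within villages the blocking could be far more complete and the gain smaller. The placing of gender and age among the random effects should be corrected in either case.

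**What to change.** In Malaria incidence data analysis, or in the analysis plan before arm-level results are seen:

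- Add household elevation, derived from the recorded coordinates, as a pre-specified fixed covariate in the Poisson incidence model and in the logistic malaria prevalence model. The low/mid/high-land zone is an alternative, but it would have to be defined first. Study setting and period divides the district into 88% mid land and 12% low land, which leaves no high land.
- Fit gender and age as fixed effects.
- Add the kebele's pre-trial malaria rate only if district records from before the interventions cover all 30 kebeles. Otherwise the covariate would be missing for part of the trial.

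The cost is one extra parameter per model for a linear elevation term (two for a three-level zone), the work of deriving elevation from the coordinates, and a sentence or two of text.

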**Methods:**

A four-armed household, cluster-randomized, controlled study will be conducted to assess the combined impact of HS, LLINs and push-pull agricultural technology (PPT) against clinical malaria in children in Ethiopia. The unit of randomization will be the household, which includes a house and its occupants. A total of 838 households will be enrolled in this study. In this trial 246 households will receive LLINs and HS, 250 will receive LLINs, HS and PPT, 175 households will receive LLINs and PPT. The remaining 167 houses which receive LLINs only will be used as control. One child aged ≤14 years will be enrolled per household in each treatment and followed for clinical malaria using active case detection to estimate malaria incidence for two malaria transmission seasons.

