#### Specific objectives

i.To determine whether adding house screening of windows and doors of houses and implementing PPT reduces the rate of malaria parasite infection, parasite density, and anemia in children (aged between 5 to 14) compared to situations where only LLINs are used.ii.To assess whether the proposed interventions reduce human mosquito-interaction (human biting rates, mosquito resting density, longevity, sporozoite rates, and the entomological inoculation rate (EIR)) inside houses compared with LLINs alone.iii.To determine the incremental costs, benefits, and cost-effectiveness of adding house screening and PPT to usage of LLINs.iv.To assess the economic, social, and environmental feasibility of the combined intervention of house screening, LLINs and PPT.

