### Eligibility criteria

The study population will be all households that are found in the rural areas of Jabi-Tehnan district having at least one child (under 14 age) in their family.

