### Study endpoints/outcomes

#### Clinical evaluations

The main outcomes of the clinical study will be the malaria incidence, splenomegaly, and anaemia. Thus, the baseline clinical survey of all study children will take place between Sept and Oct 2020 to determine the clinical parameters. As part of the follow up, starting from Nov 2020, trained health extension workers will visit the house of each child and take data of clinical symptoms, temperature, and splenomegaly (sign of spleen enlargement). While monthly follow up of the child continues throughout the 2 years of study period (Sept 2020 to Dec 2022) for documentation of any malaria incidence, blood testing of the entire cohort of the study children will be repeated at the end of each rainy season (Sept/Oct 2021) and Sept/Oct 2022). In between the annual clinical surveys (i.e., at the time of monthly follow up), blood testing will be done only to children who develop fever to minimize community fatigue development. Temperature measurement, RDT testing, blood haemoglobin measurement, blood sample collection for microscopy will be conducted by a licensed laboratory professional following the WHO guideline [44].

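### The only anaemia grading rule covers ages 6 to 59 months, while the anaemia objective concerns ages 5 to 14, so the rule grades nobody in the objective's population

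*Protocol article*

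**What the plan says.** Under Clinical evaluations the article states: "The main outcomes of the clinical study will be the malaria incidence, splenomegaly, and anaemia". Specific objective (i) asks whether the added interventions reduce "anemia in children (aged between 5 to 14) compared to situations where only LLINs are used".

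The anaemia analysis is described under Statistical methods, in the subsection Malaria incidence data analysis. It opens with a general statement: "The prevalence of anaemia among the study participants (children) will be analysed using the guideline developed by world health organization". The next sentence says how this will be applied. It covers "all children between 6 and 59 months of age, whose Hb level is recorded between" the following: "10.0–10.9 g/dl, 8.0–9.9 g/dl and less than 8.0 g/dl will be graded as mild, moderate, and severe, respectively". No cut-off for any other age appears in the article. Epidemiological data collection methods adds only that study children are graded by their haemoglobin level.

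The three grades are then added together to classify community anaemia prevalence (severe above 40%, moderate at 20 to 39.9%). Anaemia prevalence is compared between intervention and control houses with a multilevel mixed-effects logistic model.

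The age of the children is described differently elsewhere. The abstract says "One child aged ≤14 years will be enrolled per household in each treatment". Eligibility criteria asks for households "having at least one child (under 14 age) in their family". Neither gives a lower age limit.

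**The concern.** A prevalence comparison needs a case definition for every child in its denominator. The article states one for an age group that lies wholly below the age group of its own objective. This is not a detail left to a fuller document, because the article states a rule and that rule conflicts with the objective.

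An analyst working from the text has three choices: analyse only the under-fives, apply the 6 to 59 month bands to everyone, or take bands for older children from the cited guideline. Each gives a different numerator or denominator for a main outcome, and the choice could be made after the data are seen. The literal choice, under-fives only, would answer a question about children whom the objective does not cover.

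**Working it through.** The plan offers no figure to reproduce on this point. The check compares age ranges in completed months.

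**Inputs**
- Grading rule: 6 to 59 months, which is 54 completed months (Malaria incidence data analysis).
- Objective: 5 to 14 years. This is 60 to 179 months if 14 means 14 completed years, or 60 to 167 months if it means up to the 14th birthday (Specific objectives).
- Enrolment: 14 or younger, 0 to 179 months (abstract, Methods); under 14, 0 to 167 months (Eligibility criteria).
- 838 households with one child each (abstract, Methods).
- Surveys of the whole cohort from Sept/Oct 2020 to Sept/Oct 2022, 24 months apart (Clinical evaluations).

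**Step 1: overlap of rule and objective.** The rule ends at 59 months and the objective starts at 60. The overlap is 0 months under either reading of the upper limit, so the rule grades 0% of the objective's population.

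**Step 2: share of the wider enrolment range that the rule covers.** The article gives no age distribution. With uniform ages (assumed):

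| Enrolment range | In 6–59 months | Aged 5 or over, no stated grade |
|---|---|---|
| 14 or younger | 54/180 = 30%; 0.30 × 838 = 251 | 120/180 = 66.7%; 559 |
| Under 14 | 54/168 = 32.1%; 269 | 108/168 = 64.3%; 539 |

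The remainder, 28 and 30 children respectively, would be under 6 months and also have no stated grade. These counts move in proportion to the true share: a share of 20% gives 168 gradable children and a share of 40% gives 335. If enrolment follows the objective, the number is 0.

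**Step 3: change over follow-up.** A child aged 36 to 59 months at baseline is 60 months or older 24 months later. That is 24 of the band's 54 months, so 24/54 = 44% of the children graded at baseline would have left the band by the last survey under the same assumption. Children under 6 months at baseline would enter it. In a fixed cohort, the children in the band at the last survey are those who were 0 to 35 months at baseline: 36/180 = 20% (168 of 838) or 36/168 = 21.4% (180 of 838). Replacement of children, which the article allows, would change the ages further.

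**Step 4: where the rule is used.** Both the community prevalence class and the logistic model need anaemia defined as present or absent. For ages 5 to 14 the article gives no definition for either.

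**The case against.** The strongest reply is that the governing sentence is the general one: anaemia in all study children is to be analysed by a cited guideline. On that reading the 6 to 59 month bands are only one application, and a condensed article may leave the other ages to its source. This softens the point but does not remove it. The sentence with the bands is introduced as the consequence of following the guideline, it names a single age group, and that group is not the one in the objective.

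Four stronger readings are tempting, and the article does not support them.
- A reader might infer that no enrolled child can be graded, so that the comparison is empty. That would hold only if enrolment were restricted to ages 5 to 14. The abstract and the eligibility criteria set no lower limit, and one child per house is chosen at random, so under-fives can be enrolled.
- A reader might infer that the 6 to 59 month bands would misclassify older children. The guideline is not shown, no cut-off for older children appears in the article, and the article does not say that it will apply these bands to them.
- A reader might count three competing enrolment criteria. One statement is an objective, one is a household criterion, and only the abstract gives the age of the enrolled child. The conflict is between objective and enrolment.
- A reader might infer that the arms would differ in age. Allocation is randomised, so age is balanced in expectation, and the article names age as a factor to control. The problem is which children are classified.

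It also stands that the malaria incidence comparison does not use haemoglobin grading, that the trial is sized on malaria prevalence, and that the abstract's list of end points omits anaemia. This limits the severity.

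**Conclusion.** The concern holds in a bounded form. The stated grading rule covers 0% of the objective's age range; this follows from the two age ranges alone and needs no assumption. Under the wider enrolment ranges the rule covers only children of 6 to 59 months. The figures of 30% to 32% at baseline and 20% to 21% at the last survey are illustrative. They rest entirely on uniform ages, and the later pair also on a cohort without replacement.

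The consequence is that, followed literally, a main clinical outcome would be compared in a subgroup that lies outside its objective and changes from survey to survey. The malaria outcomes are unaffected, and haemoglobin values will be recorded, so nothing is lost if the rule is corrected before analysis. This is a point that should be fixed; it does not threaten the trial as a whole.

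**What to change.** 1. State one age range, with lower and upper limits in completed years or months, and use it in the abstract, Specific objectives and Eligibility criteria.
2. Replace the 6 to 59 month sentence under Malaria incidence data analysis with a rule for all enrolled ages, for example: *At each survey every enrolled child, including any replacement child, will be classified by the cited guideline's haemoglobin band for the child's age at that survey; the bands for all enrolled age groups are tabulated.* If the guideline has no band for some enrolled age, say that those children are left out of the anaemia denominator.
3. Keep anaemia prevalence in the planned mixed-effects logistic model, and base the community prevalence class on the same definition. The defect does not require a different main measure. Moving to mean haemoglobin would change the question that the objective asks.

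The cost is wording and minor programming. Haemoglobin measurement is already planned for the annual surveys. The only added need is each child's age at each survey, recorded finely enough to place the child in the right band.
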